## Abstract

**Background:**

Despite a burgeoning interest in using interprofessional approaches to promote effective collaboration in health care, systematic reviews find scant evidence of benefit. This protocol describes the first cluster randomized controlled trial (RCT) to design and evaluate an intervention intended to improve interprofessional collaborative communication and patient-centred care.

**Objectives:**

The objective is to evaluate the effects of a four-component, hospital-based staff communication protocol designed to promote collaborative communication between healthcare professionals and enhance patient-centred care.

**Methods:**

The study is a multi-centre mixed-methods cluster randomized controlled trial involving twenty clinical teaching teams (CTTs) in general internal medicine (GIM) divisions of five Toronto tertiary-care hospitals. CTTs will be randomly assigned either to receive an intervention designed to improve interprofessional collaborative communication, or to continue usual communication practices.

Non-participant naturalistic observation, shadowing, and semi-structured, qualitative interviews were conducted to explore existing patterns of interprofessional collaboration in the CTTs, and to support intervention development. Interviews and shadowing will continue during intervention delivery in order to document interactions between the intervention settings and adopters, and changes in interprofessional communication.

The primary outcome is the rate of unplanned hospital readmission. Secondary outcomes are length of stay (LOS); adherence to evidence-based prescription drug therapy; patients' satisfaction with care; self-report surveys of CTT staff perceptions of interprofessional collaboration; and frequency of calls to paging devices. Outcomes will be compared on an intention-to-treat basis using adjustment methods appropriate for data from a cluster randomized design.

**Discussion:**

Pre-intervention qualitative analysis revealed that a substantial amount of interprofessional interaction lacks key core elements of collaborative communication such as self-introduction, description of professional role, and solicitation of other professional perspectives. Incorporating these findings, a four-component intervention was designed with a goal of creating a culture of communication in which the fundamentals of collaboration become a routine part of interprofessional interactions during unstructured work periods on GIM wards.

**Trial registration:**

Registered with National Institutes of Health as NCT00466297.

## Background

Interprofessional education has been promoted internationally [1,2] and nationally [3,4] by policy makers as a means to improve collaboration and service delivery. It is often argued that if individuals from different professions learn together their professions will collaborate more effectively, improving care and the delivery of service. This argument has strong appeal, and as a result, there has been a steady growth of interprofessional education within the health and social care systems in the United Kingdom, the United States, continental Europe, Australia and more recently Canada [5]. However, findings from systematic reviews continue to report that there is only limited evidence that interprofessional education has an impact on improving interprofessional collaboration, patient care, patient-centredness or patient outcomes [6-8].

Funded by Health Canada, the SCRIPT Programme (Structuring Communication Relationships for Interprofessional Teamwork [9]) seeks both to advance the evidence base on interventions to achieve interprofessional education for collaborative patient-centred practice (IECPCP) and to achieve sustainable transformation in the conduct, learning and evaluation of interprofessional teamwork in the Toronto Academic Health Sciences Network (TAHSN), the partnership between the University of Toronto and its fully affiliated health care institutions.

### Creating a culture of collaborative communication

We developed an intervention with an aim of creating a culture of *interprofessional collaborative communication*. Whereas communication most generally is the exchange of information between individuals, our goal is to encourage the kind of communication that fosters collaborative working relationships between professionals. The intervention is designed to promote the kind of communicative exchange that would encourage joint problem solving and provision of excellent interprofessional patient-centred care. Despite the importance of information exchange between professionals, our emphasis is on what comes next: putting the information together to arrive at joint solutions and deeper understandings.

We assume that when a professional provides another with a plan or problem and has the opportunity to explicate or query a colleague's point of view, opportunities for new and more effective ideas or solutions emerge. Here, we subscribe to the principle that 'the whole is greater than the sum of its parts.' When collaborative communication is effective, the yield for the patient will be greater than if a single professional manages their care in isolation.

Collaborative communication in our model is both intentional and opportunistic. It is purposeful as health care professionals will determine the context in which the collaborative communication exchange is warranted and with whom. At minimum, one other person (from another profession) is required to make this fit the criterion of 'interprofessional.' However there is no upper limit on the number of professionals, and indeed patients or family members may be included in the collaborative exchange. The main criterion guiding whether or not professionals choose to seek out input from their colleagues is that without collaborative communication, the problem could not be solved uniprofessionally. The purpose and context of the collaborative communication are entirely decided by the professionals engaged in the activity.

The general internal medicine (GIM) project has investigated interprofessional behaviours in hospital clinical teaching teams (CTTs) by using naturalistic observations and in-depth interviews. These data were foundational for the design of a workplace-based staff intervention that is intended to promote interprofessional collaborative communication.

There were two important findings from our preparatory qualitative observations of ward interactions. First, there is a high turnover rate of the medical staff on GIM wards due to their professional rotations. Turnover presents a major challenge for both clinical (medicine, nursing, other health professionals) and administrative staff and trainees in relation to learning the names, roles, and scopes of practice of individuals working beside them [10]. Second, GIM teams have distinctive norms and established mechanisms for facilitating formalized and planned interprofessional communication and collaboration, such as daily interdisciplinary rounds. However, none of the GIM divisions we observed has developed a normative procedure for interprofessional communication and collaboration during *unstructured*, *unscheduled *work periods.

Moreover, our research showed that important characteristics of communication and collaboration behaviours are problematic in *opportunistic *encounters. Four areas were notable:

1. Mutual interpersonal knowledge of given names and surnames is often absent. Staff members perceive that they do not know very many others' names, and that their own names are usually unknown to others;

2. Mutual interpersonal knowledge of another's occupational title, professional role, or educational credentials is absent or ambiguous;

3. Interprofessional patient-related interactions are not commonly marked by sharing of unique, profession-specific knowledge bases, e.g., care-plan activities or diagnostic questions; clinical health management concerns are sequestered;

4. Interprofessional patient-related interactions pass information along routes that are seemingly one-way, unidirectional pathways; there is little reciprocity.

Hence, the intervention design focuses on improving interprofessional communication and collaboration outside of structured meetings, specifically to increase the quality of opportunistic encounters between professionals.

A cluster randomized design is the only possible trial design in our setting. Department of Medicine managers and nursing and professional leaders organize staff members into functional GIM teams. We can not define teams as intervention or control teams and then randomize individual staff members to teams; randomization at the individual level would require us to deconstruct and re-construct teams according to random assignments, an impossible process. Individual randomization to intervention status without team randomization would result in contamination as intervention group staff members worked alongside control group staff members.

## Methods

### Participants and setting

General internal medicine is organized as a 'division' in hospitals of the TAHSN, housed within Departments of Medicine. In many hospitals, GIM divisions have long been organized into groups known as clinical teaching teams. Teams serve goals related to patient care, education, collegiality, and administration.

GIM divisions in TASHN hospitals are composed of between 200 and 300 staff and students. The medical staff of a CTT is composed of a staff physician, medical residents, and clinical clerks. The number of medical trainees working in a clinical teaching team varies at any particular time between about five and nine. Usually, it includes one senior resident, a second- or third-year post-licensure medical resident (PGY2), two first-year medical residents (PGY1), one pre-licensure medical student in the fourth year of medical school (fourth-year clinical clerk), and two or three pre-licensure medical students in the third year of medical school (third-year clinical clerks).

Medical teams work with groups of non-physician health professionals. In Ontario, Canada, these are full-time, part-time, temporary, or casual employees of the hospital. The GIM CTTs in our trial employ professionals in all of these statuses and they may or may not work exclusively in wards of the GIM division. A typical team may include a variety of professions, most commonly nursing, physical therapy, occupational therapy, social work, diet and nutrition, and pharmacy. In the TAHSN system, the non-medical, non-nursing professions have traditionally been called 'allied health professions' and their individual practitioners are known as 'allied health professionals,' or 'allied staff.' These professions and their members are regulated under the Regulated Health Professions Act of the province of Ontario and their respective disciplinary colleges are licensed by laws of the province of Ontario, Canada.

The SCRIPT study is expected to operate in twenty medical teams making up the GIM divisions of five TAHSN hospital sites. Inclusion criteria for hospitals are: the hospital corporation or its site(s) must be a member of the TAHSN and the site must have a general internal medicine service within its Department of Medicine. A medical team is eligible if it has a regularly scheduled rotation of attending staff physicians and residents; has both nursing and allied health professional staff members working with it regularly; and is not a specialized team providing devoted care to particular medical or surgical cases or conditions, e.g., stroke.

### Intervention

The intervention is a four-step collaborative communication protocol, a quasi-script for face-to-face, collaborative interprofessional interaction. We will ask GIM staff members and trainees to use the four following steps when they have face-to-face patient-related interactions with individuals whom they know (or believe) are members of a different professional group than their own:

1. Name – Introduce oneself to the member(s) of the other profession by name;

2. Role – State to the other interactant(s) one's own professional role in the team or GIM division and describe it with respect to the target patient under discussion;

3. Issue – Share with the member(s) of the other profession one's unique, profession- and training-specific issues, problems, or plans relating to the target patient under discussion; and

4. Feedback – Elicit interaction-specific feedback from the other participant(s) in the interaction by using prompts such as, "Do you have any concerns?" or, "Is there something else I should consider?"

These four steps illustrate our approach to two key intervention goals. First, by continuously introducing oneself by name and role in relation to a specific patient, the typical social barriers in a rapidly changing GIM division – role confusion and anonymity – are reduced. Second, by sharing one's professional perspective and eliciting a collegial point of view, opportunities to solve a patient care problem and/or extend care beyond the limits of uniprofessional practice are elevated.

For GIM medical staff and trainees, intervention implementation will begin in the orientation of a new rotation of medical residents by a team's attending staff physician. This orientation is regularly scheduled during the first week of the rotation. We will enlist the attending physician of each GIM division's two intervention-group medical teams to explain and promote the importance of each of the above mentioned communication behaviours to his or her resident team physicians. Likewise, the same promotional activity will be offered by other professional staff leaders in the intervention CTTs to the professionals who report to them, nurses and allied health professionals. For all professional leaders there will be frequent, opportunistic reinforcements in formal or informal meetings, in one-to-one or group uniprofessional or interprofessional settings.

Implementation will be augmented in the following ways. First, we will establish a broad network of core "faculty advocates" in the intervention teams. Advocates will act as role models and provide direct verbal instruction to their colleagues on the team. We will ask the Patient Care Managers (or equivalents) on intervention teams to enlist the support of staff members who are willing to champion the intervention. Second, advocates will receive initial training about the intervention etiquette from research staff. Third, researchers will provide consultation to advocates to support them in the training, implementation, and uptake goals. Finally, we will use email as a delivery channel to inform advocates of the latest research results and to offer suggestions for reinforcement throughout the duration of the study. The responsibility for implementation of the intervention therefore is shared by researchers and staff-participants in GIM. We anticipate that these combined initiatives will promote increased buy-in and uptake among front line staff-participants in the GIM experimental teams.

In each intervention CTT we expect that thirty minutes will be required to explain the intervention to professional leaders and to field questions. We expect it will take ten minutes of discussion by each of the professional leaders with their trainee or reporting colleagues in each profession. We expect that the time cost of reinforcement will be fleeting, and might occur two or three times per week, at such times as regular rounds or meetings within professions, in interprofessional team meetings, in individual supervision and education meetings, and in opportunistic conversations.

The intervention will run approximately eight weeks in the intervention CTTs. In this time it will expose two rotations of staff and resident physicians and the other health professional staff with whom they work on the teams to the communication and collaboration script. At each hospital site, staff and patient outcomes related to each of the two intervention and control health care teams will be compared.

### Qualitative data collection

The use of qualitative methods to support the development and evaluation of RCTs for complex interventions to improve health, including observational ethnographic research and individual in-depth interviews, has been promoted by the UK Medical Research Council [11]. Non-participant ethnographic research [12,13] characterized by focused, short-term field observations [14], shadowing [15], and qualitative, semi-structured interviews will be conducted during the intervention implementation period by experienced qualitative researchers.

Researchers will position themselves unobtrusively throughout the wards during brief, focused field visits and will collect descriptive and reflective data on verbal and non-verbal interprofessional interactions. Descriptive observation notes will report as closely as is possible the verbatim conversations and sequences of activities that occur. They will identify those present only by professional or occupational role (i.e., no names or other identifiers will be used). Reflective notes will record the researcher's attributions of meanings of the observed interactions.

Shadowing will occur with a purposive sample of GIM CTT staff from a range of professions (e.g., social workers, staff physicians, registered nurses) and training levels (e.g., pre-licensure physiotherapy students, post-licensure medical students). The number of shadowed participants will be 6–7 participants per team, an adequate number to achieve saturation within a homogenous subgroup [16]. Shadowing will involve recording for continuous one-hour periods the behaviours, interactions, and activities of the participant in public areas where patient care is organized or discussed; the researcher will not enter patients' rooms and will avoid observing and recording patient-healthcare provider interactions that could occur outside of rooms, e.g., in halls, lounges, and other common areas.

On the ward floors, there will be no observation-related interruptions to team staff and they will experience no time cost. Shadowing will be arranged with staff members based on mutual availability and convenience, usually between 8:00 a.m. and 5:00 p.m.

During the shadowing sessions, the researcher will ask the participant to explain what he or she is doing in order to prompt not only a running commentary of the particular task being performed, but the social and organizational reasons for the behaviour [15]. The researcher will also attend to the presence and effect of the four steps of the intervention within each interprofessional interaction observed during the shadow period.

Interviews will be done with a purposive sample of GIM CTT staff. The intent is to more fully understand the culture of interprofessional communication among the specific teams, to further explore phenomena identified during observations or shadow periods, and to understand and document activities related to the adoption of the intervention and changes in practice. Interviews will be semi-structured and will be initially developed from the existing literature on interprofessional education. However, interviews will be individualized to allow the researcher to posit questions based on the ongoing observational and shadowing data, as well as to follow up on spontaneous participant comments during interview. Interviews will continue until researchers determine that saturation has been reached, that is, until researchers feel that no new information will be garnered through further interviews [16,17].

The use of qualitative observational and interview techniques will enable researchers to document and monitor complex interactions between the intervention, its settings, and its adopters [18]. In addition, direct observation produces rigor when combined with other methods, for example, it can illuminate discrepancies between participants' quantitative and qualitative self-reports of interprofessional collaborative communication practices and their actual communication and interaction patterns [19].

### Ethics oversight and informed consent

The SCRIPT GIM project has three phases: (1) ethnographic observation and intervention design, (2) pilot study, and (3) cluster randomized controlled trial. Ethics approval will be requested at all participating hospitals and the University of Toronto research ethics boards for each phase. To date, approval was given by three hospitals and the university for phase 1 ethnographic observations and intervention design. Approval was granted by one hospital and the university for the phase 2 pilot study. We received ethics approval from two hospitals and the university to conduct phase 3, the cluster RCT.

Notices will be posted describing the presence and operation of a research program in GIM. The study will be described by the senior hospital staff from each profession in each clinical teaching team at scheduled staff meeting times like bullet rounds and Kardex. They will inform staff members of the presence of the SCRIPT researchers in the GIM teams and indicate that staff members who do not wish to be a subject of research observations can make such a declaration to SCRIPT's observers. Subsequently, observers will not approach these individuals during shadowing sessions and will not record any observations about them. Staff members will not be shadowed into patient rooms and no identifiable patient information will be recorded. Fieldwork observers will not attempt to gain access to any written, identifiable personal health information.

### Objectives: hypotheses

The SCRIPT Programme aims to create a cultural shift in the way health professionals communicate and collaborate in GIM hospital teams. There are three objectives for the SCRIPT Programme, the first two of which have been successfully completed. They are:

1. To assess interprofessional communication and collaboration;

2. To create an intervention – a tool or other process – that improves interprofessional communication and collaboration;

3. To implement and evaluate the effects of the intervention on outcomes.

The objective of the trial is to implement and evaluate the effects of an intervention aimed at enhancing collaborative communication between professionals and improving patient-centred care.

The research hypotheses for trial-related quantitative outcomes are:

1. Patients who are discharged from intervention teams will be less likely to be readmitted to hospital than patients discharged from control teams;

2. Mean time to readmission will be longer for patients discharged from intervention teams than for patients discharged from control teams;

3. Patients who are cared for by intervention teams will have shorter mean lengths of stay than patients in control teams;

4. Survey-measured perceptions of interprofessional collaboration will be higher among staff members of intervention teams than staff members of control teams;

5. Patients will report higher satisfaction with care after being treated by intervention teams than by control teams;

6. There will be an association between the number of calls to staff members' paging devices and team status; intervention-team staff members will receive fewer pages;

7. Adherence rates to evidence-based best practices for prescription drug therapy of geriatric acute-care inpatients will be greater among intervention teams than control teams.

Qualitative data are not collected in confirmation or denial of a hypothesis, but in explanation of the findings of the intervention trial. These data will be used to understand staff perceptions of the effects of the intervention and the barriers and catalysts for its implementation.

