The readmission dataset will be constructed with criteria similar to van Walraven et al. [20]. Patients will be identified as eligible for the readmission pool if they had a nonelective admission to one of the participating sites' GIM divisions through its medical or surgical department, were discharged alive from the participating site's GIM division in the same index admission, and had a nonelective medical or surgical readmission to any Ontario hospital within either 7 days or 30 days of discharge of the index admission. Patients will be excluded if they were admitted from or discharged to another hospital in the index admission; if they had no patient identifier or an invalid identifier; if they lacked key information; or if they exceeded the 99^th ^percentile of distributions of the following variables for all Ontario hospitals: hospital length of stay, number of previous hospitalizations, number of follow-up visits, or case resource consumption.

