### Sample size

Sample size and power were estimated with PASS software [27]. The trial's primary outcome is the proportion of unplanned hospital readmissions among patients discharged from a GIM team. We assume an intracluster correlation coefficient of 0.01. In this trial we expect there will be in excess of 200 patients admitted into each clinical teaching team in the 2-month intervention period. In total there will about 4000 patients admitted into and discharged from twenty clusters (teams) over five hospital sites. We assume that a typical rate of readmission among GIM patients within 30 days after discharge is ten percent. When significance is set at p < 0.05, the trial would have 93% power to detect a 5.0 percentage-point lower rate of unplanned hospital readmission among patients discharged from intervention CTTs than control CTTs (i.e., 10% versus 5%). A 5.0 percentage-point difference would represent a fifty-percent difference in readmission rates between intervention and control team patients.

If the rate of readmission within 30 days of discharge from GIM treatment is five percent, and if the intracluster correlation coefficient is 0.01, then the trial has 67% power to detect a 2.5 percentage-point lower rate of readmission among patients discharged from intervention teams. Again, this is a fifty-percent difference (i.e., 5% versus 2.5%).

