#### Readmission

Two patient follow-up periods will be investigated for unplanned hospital readmission: the primary outcome, 30 days post-discharge, and a secondary outcome period of seven days post-discharge. Discharge records will be examined for patients discharged to home between one week after intervention period commencement and one month after intervention conclusion. Readmission proportions will be calculated for patients discharged from intervention and control group teams. The significance of the difference in proportions will be tested with chi-square and association statistics adjusted for the cluster randomized design [29-32]. The primary aim of the trial is to estimate the population-level intervention effect on binary-coded readmission outcomes; consequently, generalized estimating equations will be employed to control for clustering.

Some patients could have multiple hospital admissions, possibly to different hospitals during the study period. Furthermore, some of the admissions may qualify as an "outcome" while others do not. This situation raises a possibility that patients could change clusters (teams) during the trial, by being readmitted to a different GIM team within the same hospital that discharged them earlier in the intervention period. Therefore, a patient will contribute an observation to the analysis only from their first admission during the intervention period. If the readmission is to a different hospital than the index admission, then the readmission is 'credited' to the hospital of the index admission.

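### Hypothesis 2, as written, compares mean time to readmission among readmitted patients only, so its direction is not a valid sign of benefit

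*Protocol article*

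**What the plan says.** The section Objectives: hypotheses of the Protocol article lists seven quantitative hypotheses. The first concerns the likelihood of readmission. The second is separate and concerns timing: "Mean time to readmission will be longer for patients discharged from intervention teams than for patients discharged from control teams". It gives no time horizon and no value for patients who are never readmitted.

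Three other places bear on it:

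- **Outcomes: measurement, Readmission data.** To enter the readmission pool, a patient must have had a nonelective index admission, been discharged alive, and "had a nonelective medical or surgical readmission to any Ontario hospital within either 7 days or 30 days of discharge of the index admission".
- **Statistical methods, Readmission.** Follow-up has two lengths: "the primary outcome, 30 days post-discharge, and a secondary outcome period of seven days post-discharge". The stated aim is to "estimate the population-level intervention effect on binary-coded readmission outcomes", using proportions, cluster-adjusted chi-square and generalized estimating equations. Censoring, survival methods and restricted means are not mentioned there or elsewhere in the article.
- **Sample size.** "We assume that a typical rate of readmission among GIM patients within 30 days after discharge is ten percent". The target effect is 10% versus 5%, with a second scenario of 5% versus 2.5%.

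**The concern.** A time to readmission exists only for patients who are readmitted. With 30 days of follow-up and the plan's own rates, 90 to 95% of control patients have none, and more still in the intervention arm if the intervention works. A plain mean therefore describes the minority who had the event.

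Readmission occurs after randomization and is what the intervention is meant to change. The readmitted patients in the two arms are thus selected by the effect itself, and randomization does not make them comparable. Such a mean says when readmissions happen given that they happen. It does not say whether patients stay out of hospital longer, which is the natural meaning of the hypothesis. It also sits poorly with the intention-to-treat comparison promised at the start of Statistical methods.

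At stake is how one pre-stated hypothesis is read. A real benefit could appear as no effect or as an adverse effect, and an increase in late readmissions could appear as support.

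**Working it through.** **Inputs from the plan (Sample size; Randomization).** 20 teams, 10 per arm; 200 patients per team, so 2000 per arm; intracluster correlation 0.01; 30-day readmission 10% versus 5% (second scenario 5% versus 2.5%); significance level 0.05.

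**Assumptions added here.** The plan does not give the timing of readmissions within the 30 days, so several shapes are used. Death after discharge is ignored because no rate is given.

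**1. The plan's own figure.** The plan gives no figure for mean time to readmission. Its power figures confirm that the inputs are read correctly. Design effect = 1 + (200 − 1) × 0.01 = 2.99. Effective size per arm = 2000 / 2.99 = 669. A two-sided pooled test of two proportions gives power of 93.6% (plan: 93%) for 10% versus 5%, and 67.3% (plan: 67%) for 5% versus 2.5%. Both reproduce.

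**2. Mean among readmitted patients, proportional reduction in hazard.** With S(t) the proportion not yet readmitted and A the area under S from 0 to 30,

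E[T | T ≤ 30] = (A − 30 × S(30)) / (1 − S(30)).

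For a constant hazard L = −ln(1 − p)/30, A = p / L.

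- p = 0.10: L = 0.003512, A = 28.474; mean = (28.474 − 27.0) / 0.10 = 14.74 days.
- p = 0.05: L = 0.001710, A = 29.244; mean = (29.244 − 28.5) / 0.05 = 14.87 days.

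Front-loaded Weibull hazards give nearly the same difference:

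| Shape | Readmitted only: control, intervention | Difference | All patients, area to day 30: control, intervention | Difference |
|---|---|---|---|---|
| 1 | 14.74, 14.87 | 0.13 | 28.47, 29.24 | 0.77 |
| 0.75 | 12.59, 12.73 | 0.14 | 28.26, 29.14 | 0.88 |
| 0.5 | 9.74, 9.87 | 0.13 | 27.97, 28.99 | 1.02 |

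About 200 control patients (2000 × 0.10) and 100 intervention patients (2000 × 0.05) would be readmitted. With a standard deviation of about 8.66 days (constant hazard), the standard error is 8.66 × √(1/200 + 1/100) = 1.06 days. The standardized difference is about 0.13 / 1.06 = 0.12, so power is about 5%, equal to the significance level, before any penalty for clustering.

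**3. The same halving when prevention depends on timing.** Assume that control readmissions (10%) are uniform over 30 days, with mean 15.0.

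- Only those after day 15 prevented: 5% readmitted, mean 7.5 days. The benefit looks like harm.
- Only those before day 15 prevented: 5% readmitted, mean 22.5 days.
- Harm, with 5 points of readmissions added after day 15: 15% readmitted, mean (10 × 15 + 5 × 22.5) / 15 = 17.5 days. The harm looks like benefit.

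Mean readmission-free days to day 30 in all patients have the right sign each time:

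- Control: 0.90 × 30 + 0.10 × 15 = 28.50.
- Late prevention: 0.95 × 30 + 0.05 × 7.5 = 28.88.
- Early prevention: 0.95 × 30 + 0.05 × 22.5 = 29.63.
- Harm: 0.85 × 30 + 0.15 × 17.5 = 28.13.

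**4. Censored time-to-event analysis of all patients.** Hazard ratio = ln(0.95) / ln(0.90) = 0.487. There are 300 events, and 300 / 2.99 = 100 effective events. Schoenfeld's formula gives power of about 95% (about 71% in the second scenario). This uses the plan's design effect and a normal approximation, with no allowance for the small number of teams.

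**The case against.** The hypothesis never says that the mean is taken among readmitted patients. Its population wording covers patients discharged from the teams, as in hypothesis 1, and a fuller plan could specify a censored analysis. This is true, and the restriction to readmitted patients is a reading of several sections together. But the article does more than omit a method. It names a plain mean as the quantity and makes readmission a condition of entering the dataset. A fuller plan would have to depart from one of these.

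A reader might infer that the whole analysis file holds only readmitted patients, so that the primary outcome fails too. The documents do not support this. The data request covers all patients treated by the listed physicians, the sample size counts about 4000 discharges, and the statistical section calculates proportions among discharged patients. The dataset criteria are best read as merging denominator and event definitions.

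A reader might also infer that mean time to readmission cannot show a benefit at all. That is too strong: the near-zero difference needs a roughly proportional reduction, and in step 3 the mean rises to 22.5 days when early readmissions are prevented. What holds is that its direction is unreliable.

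Finally, time to readmission is not among the primary or secondary outcomes in the Abstract, and the binary analysis already tests whether readmissions fall. This limits the importance of the point but does not make the stated summary sound.

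**Conclusion.** The concern holds in this limited form. Taken as written, hypothesis 2 rests on a mean within an outcome-selected 5 to 10% of patients (fewer in an effective intervention arm), and its direction is not a valid sign of benefit.

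For the plan's target effect, the mean moves by about 0.13 day under constant hazard, and by 0.13 to 0.14 day across the three hazard shapes tried. Under timing-dependent prevention with uniform control timing, it ranges from 7.5 to 22.5 days around a control value of 15.0, for the same halving of readmissions. These figures rest on assumed timing within the 30 days and ignore deaths.

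The primary 30-day binary analysis and its stated power are not affected by hypothesis 2. The change is worth making because the stated summary can mislead and a sound alternative is cheap.

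**What to change.** 1. Restate hypothesis 2 on all eligible live index discharges. Either of two measures would serve: restricted mean readmission-free time to day 30, or time from index discharge to first unplanned readmission, censored at day 30. Use cluster-robust variance by team. The plan names neither a hospital term nor a small-sample correction for its primary analysis, so the treatment of clustering needs to be stated here and not taken over by reference.
2. Reword the criteria under Readmission data so that they define the eligible index discharges, with readmission within 7 or 30 days as the outcome and not a condition of entry. Non-readmitted patients then visibly stay in the dataset.
3. Treat death after discharge as a competing event where it is known. The discharge data may not capture deaths outside hospital, and the article names no other source, so incomplete capture should otherwise be noted as a limitation.

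The cost is the wording of one hypothesis, one analysis and one dataset definition. The discharge database already supplies the index and readmission dates. Only the deaths could need an additional source.
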